### Data analyses

All analyses will be conducted using the intent to treat approach. The primary analysis will be adjusted only for clustering (the community effect). This adjustment for clustering also adjusts for community or site differences. A comprehensive analysis of baseline variables of the two treatment groups will be performed to assess the extent, if any, of baseline imbalances between the two groups of clusters/communities assigned to the two treatment groups, both at the individual and at the cluster levels, to determine the need for adjusting analyses. The baseline variables to be examined include: gender and socioeconomic status (SES), prevalence of exclusive breast feeding at 6 months, birth weight, maternal stature, parity, and site. Imbalances occurring at the cluster level can also be adjusted for by incorporating cluster level covariates, which may be cluster aggregated versions of the co-variables mentioned above.

For analysis of the primary outcome, the WHO Multicentre Growth Reference Study [38] will be used as a comparison. Mean Z-scores at 6, 9, 12 and 18 months for length-for-age, weight-for-age and weight-for-length will be determined as well as changes in Z-scores over 12 months. Linear growth velocity from 6-18 months of age was selected as the primary outcome measure because of its potential to be statistically more powerful than a cross-sectional comparison of length at 18 months alone.

The statistical analyses of the primary outcome and other comparison between treatment groups will use hierarchical or multi-level models to adjust for the cluster randomized design of the study. Hierarchical modeling provides a straightforward framework to accommodate adjustments for potential covariates and confounders, both at the subject level (e.g., birth weight, gestational age, gender, etc.) and at the cluster/community level (average SES at the community level, community access to prenatal and antenatal care, community exposure to other nutrition messages, etc.). For both 18-month and longitudinal outcomes, linear mixed models will be used for continuous outcomes such as growth parameters, whereas generalized linear mixed models will be used for discrete outcomes such as frequency of various nutritional intakes and incidence of morbidities.

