### Duration

At least one interim home visit was conducted between enrollment and the start of the intervention when the infant reached 6 months. The first formal assessments (anthropometry and dietary data collection) were obtained at 6 months of age. At this time, the complementary feeding intervention for both groups was initiated and continues through 18 months of age. Follow-up anthropometric assessments are conducted at 9, 12, and 18 months of age. Neurocognitive assessments are performed at 12 and 18 months. Blood samples to assess nutritional status are being obtained from a convenience sample at completion of the trial at 18 months of age.

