### Power Analyses

Based on the effect size of 0.5 standard deviation (SD) units observed in another cluster based study of complementary feeding [8], the statistical power for this study was set at 80% to detect a more conservative difference of 0.3 SD in linear growth velocity from 6 to 18 months of age between the intervention and control groups, using a two-tailed test and a 5% Type I error rate.

An ICC = 0.05 was assumed for the sample size calculation. Note that 0.05 is in the upper ranges of ICC values observed in many cluster randomized trials, and would provide the most conservative (i.e., the largest) sample size estimate. Moreover, for a given level of ICC (and Type I and II errors) in a cluster randomized study, increasing the average cluster size reduces the number of required clusters, while increasing the total sample size. This fact, coupled with the consideration that a minimum of 10 clusters are required per treatment group to credibly estimate the ICC with acceptable precision, plus the actual cluster sizes observed in ongoing GN trials, led to an estimated average cluster size of 30.

The above assumptions, an adjustment for 20% attrition over the duration of the study, plus an allowance for cluster loss because of unforeseen reasons such as natural disasters (2 per treatment group), result in a requirement of 20 clusters per treatment group, for a total of approximately 600 subjects per treatment group (40 clusters and 1200 subjects total). Thus, 10 clusters (5 per intervention arm) in each participating country, with approximately 30 subjects per cluster were necessary to achieve desired power.

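### The primary analysis of 6-18 month linear growth velocity does not use 6-month length as a covariate, although it is already measured and adjusting for it can only help precision or leave it about unchanged

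*Protocol article*

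**What the plan says.** All references are to the protocol article.

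- **Outcome and reason (Data analyses).** "Linear growth velocity from 6-18 months of age was selected as the primary outcome measure because of its potential to be statistically more powerful"; the comparator that completes the sentence is "than a cross-sectional comparison of length at 18 months alone".
- **Primary model (Data analyses).** "The primary analysis will be adjusted only for clustering (the community effect").
- **Baseline variables to be checked for imbalance (Data analyses).** "gender and socioeconomic status (SES), prevalence of exclusive breast feeding at 6 months, birth weight, maternal stature, parity, and site". Length at 6 months is not named. It is also absent from the examples of subject-level covariates given later in that section (birth weight, gestational age, gender).
- **Measurement (Duration).** "The first formal assessments (anthropometry and dietary data collection) were obtained at 6 months of age", which is when the intervention begins. Later visits: "Follow-up anthropometric assessments are conducted at 9, 12, and 18 months of age".
- **Sizing (Power Analyses).** Power was "set at 80% to detect a more conservative difference of 0.3 SD in linear growth velocity from 6 to 18 months of age", two-sided at 5%, with an ICC of 0.05, clusters of 30, 20% attrition and two spare clusters per arm. The result is 20 clusters and about 600 infants per arm.

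**The concern.** The stated reason for choosing velocity is power, but velocity is compared only with the weakest alternative, 18-month length with no use of the starting value. The natural third option is 18-month length adjusted for 6-month length or, equivalently, velocity adjusted for 6-month length. It uses the same data and is not considered.

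An unadjusted change subtracts the whole of the starting length. When the regression of 18-month on 6-month length has a slope below 1, that over-corrects: children who start shorter tend to gain more. Any chance difference between arms in 6-month length then passes partly into the estimated effect. At stake are some precision and some protection against baseline imbalance in a trial with 20 clusters per arm.

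**Working it through.** **Inputs.** From Power Analyses: difference 0.3 SD of velocity, 80% power, two-sided 5%, ICC 0.05, cluster size 30, attrition 20%, two spare clusters per arm. Assumed, because the protocol does not give them: the correlation r between length at 6 and 18 months, and the SDs s6 and s18.

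**1. The plan's own figure.** An individually randomized comparison needs 2 × (1.96 + 0.84)² / 0.3², or 175 per arm. The design effect is 1 + 29 × 0.05 = 2.45, so 175 × 2.45 = 428.75. Attrition gives 428.75 / 0.8 = 536, and 536 / 30 = 17.9, rounded up to 18 clusters. Adding 2 gives 20 clusters per arm. The figure reproduces.

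**2. The protocol's own comparison.** With equal SDs, Var(change) / Var(18-month length) = 2(1 − r). This is 1.4 at r = 0.3, 1.0 at r = 0.5 and 0.4 at r = 0.8. In general velocity wins when r > 0.5 × s6/s18, so the sentence is right for moderate or high correlations.

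**3. Change against the adjusted analysis.**

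- Var(change) = s6² + s18² − 2r·s6·s18
- Var(adjusted) = s18²(1 − r²)
- Difference = (s6 − r·s18)², which is never negative

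With equal SDs the ratio adjusted/change is (1 + r)/2. When the SD grows with age the ratio moves towards 1 and reaches it where r·s18/s6 = 1. Example: s18/s6 = 1.2 and r = 0.7 give 0.734 / 0.760 = 0.966.

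| s18/s6 | r = 0.5 | 0.6 | 0.7 | 0.8 | 0.9 |
|---|---|---|---|---|---|
| 1.0 | 0.750 | 0.800 | 0.850 | 0.900 | 0.950 |
| 1.1 | 0.818 | 0.870 | 0.921 | 0.968 | 1.000 |
| 1.2 | 0.871 | 0.922 | 0.966 | 0.997 | 0.977 |
| 1.3 | 0.912 | 0.957 | 0.991 | 0.997 | 0.917 |
| 1.4 | 0.942 | 0.980 | 1.000 | 0.980 | 0.846 |

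**4. What this means for power.** With 24 completers per cluster the design effect is 1 + 23 × 0.05 = 2.15. Unadjusted change then has 85.3% power with 18 clusters per arm (effective n = 432 / 2.15 = 200.9) and 88.7% with 20. With 18 clusters, equal SDs and the same ICC after adjustment, power = Φ(0.3 × √(200.9/2) / √ratio − 1.96). The last column reruns step 1 with the reduced variance.

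| r | Power, adjusted | Clusters per arm, plan's recipe |
|---|---|---|
| 0.5 | 93.5% | 16 |
| 0.6 | 92.0% | 17 |
| 0.7 | 90.3% | 18 |
| 0.8 | 88.7% | 19 |
| 0.9 | 87.0% | 19 |

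**5. Does clustering change the answer?** The variance of the treatment difference is (2/K)(Vb + Vw/m), with K = 18, m = 24, ICC 0.05 at both ages and equal SDs. Between-cluster correlations ran from 0.5 to 0.95 and within-cluster correlations from 0.5 to 0.8. One common slope gave ratios to change of 0.75 to 0.98, except 1.002 in the extreme case (between 0.95, within 0.5). Giving the cluster mean of 6-month length its own coefficient kept every ratio between 0.75 and 0.94. That costs one cluster-level degree of freedom out of 36 to 40 clusters.

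**6. Baseline imbalance.** With equal SDs, an imbalance d in 6-month length shifts the unadjusted change by (1 − r)d, against the arm that starts longer. For r = 0.7 and d = 0.1 length SD this is 0.03 length SD. The SD of change is √(2 × 0.3) = 0.775, so the shift is 0.03 / 0.775 = 0.039 velocity SD, or 13% of the 0.3 target. If 6-month length also has an ICC of 0.05, the SE of the between-arm difference with 600 per arm is √(2 × 2.45 / 600) = 0.09 SD. An imbalance of at least 0.1 SD either way would then arise by chance about 27% of the time, before any benefit from matching clusters on stunting.

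**The case against.** The strongest reply is that nothing in the plan is wrong. Four parts of it stand.

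- **The sentence is not false.** A reader might infer that the protocol claims velocity is the most powerful choice. It claims only a potential advantage over unadjusted 18-month length, which holds for r above 0.5 with equal SDs.
- **Velocity is not defined in the article.** Treating it as a 6-to-18-month change is an inference from the term and from the clustering-only adjustment. With visits at 6, 9, 12 and 18 months it could be a modelled slope, for which (1 + r)/2 is not the variance ratio. The section also reports attained and changed Z-scores ("Mean Z-scores at 6, 9, 12 and 18 months for length-for-age, weight-for-age and weight-for-length will be determined as well as changes in Z-scores"), but leaving the exact scale to an analysis plan is normal for an article and is no fault here.
- **The gain may be small.** The 25% figure belongs to r = 0.5 with equal SDs, exactly where velocity stops beating 18-month length.
- **Later adjustment is not excluded.** The baseline list is open-ended and serves to decide whether adjusted analyses are needed.

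A reader might also infer that adjustment would cure bias from recruiting infants after open allocation. The documents do not support that. Under chance imbalance the change score is unbiased over repeated randomizations, and adjustment helps precision and the result conditional on the imbalance. Under selective recruitment neither analysis is guaranteed unbiased. The plan has some protection: clusters were matched on stunting rate, and infants were approached in the order of a randomly selected list (Cluster Randomization and Sampling; Study Subjects and Enrollment).

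What the reply does not meet is that restricting the primary analysis to clustering is a stated decision, not an omission. It leaves out a covariate that is already measured and has essentially no precision cost.

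**Conclusion.** The point holds as an efficiency improvement, not as an error. If velocity is analysed as change, adjusting for 6-month length is essentially never less precise. Its size depends on quantities that the protocol does not give: a 5-25% lower variance for r from 0.9 to 0.5 with equal SDs, and about 0-8% at r of 0.7-0.8 if the SD grows 10-30% with age. It can be nil.

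Adjustment also reduces the effect of chance imbalance in 6-month length, by about 0.04 velocity SD per 0.1 SD of imbalance at r = 0.7 with equal SDs.

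It would be tempting to conclude that the trial is underpowered. It is not shown to be: the stated sample size reproduces, and with 24 completers per cluster the unadjusted analysis has about 85-89% power on the plan's own assumptions.

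**What to change.** Keep velocity as the primary outcome. Prespecify 6-month length, on the same scale as the outcome and optionally with its cluster mean, as a covariate in the primary mixed model. Keep the analysis adjusted only for clustering as a sensitivity analysis.

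The hypothesis does not change. With 6-month length in the model, the treatment effect on change equals the treatment effect on 18-month length, because only the coefficient of 6-month length moves (by 1). Dividing the change by a common 12 months merely rescales the effect.

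The cost is one covariate (a second if the cluster mean is used) and a sentence of wording, settled before outcomes are compared by arm. No new data are needed, and no infants are lost, since a change already requires the 6-month value.

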## Discussion

### Administrative Structures

#### Trial Steering Committee

A Complementary Feeding Steering Committee provided guidance for the development of the study protocol and study procedures in the preparatory phase of the trial, and provides ongoing scientific oversight. The committee meets in-person two times per year to discuss study progress, problem-solve, and provide guidance where necessary.

#### Data Monitoring Committee

As per the NIH Policy for Data Safety and Monitoring, the trial is overseen by a data monitoring committee (DMC). The DMC has the responsibility to ensure the safety of study participants and the validity and integrity of data collected. The DMC determines the safe and effective conduct and recommends conclusion of a trial when significant benefits or risks have developed or the trial is unlikely to be concluded successfully.

#### Research ethics

This research study was reviewed for approval by the Institutional Review Board (IRB) of each participating institution. Annual reviews are conducted as per each institution's standard review procedures. The IRBs are registered at OHRP with FWAs. Safety and efficacy analyses are performed at scheduled intervals based upon age (after every 100 infants reached one year of age) and the completion of study participation. All participants gave informed consent prior to enrollment into the study.

#### Implications

A strong evidence base will be required to mobilize action at local, national and international levels to develop local meat production at a household or community level. The lyophilized beef greatly simplified the implementation of this efficacy study, but it is recognized that the provision of this product is not sustainable. However, positive results from this study will provide an impetus to advocate for development of locally sustainable means and incentives to modify current practices so that the older infant and toddler, the primary beneficiaries, are provided some form of meat as a complementary food.

Trial registration: NCT01084109

## Abbreviations

ASF, Animal source foods; ASQ, Ages and Stages Questionnaire; ASQ-SE, Ages and Stages Questionnaire - Social Emotional; BSID, Bayley Scale of Infant Development; CF, Complementary feeding; DCC, Data coordinating center; DMC, Data monitoring committee; DMS, Data monitoring system; FWA, Federal Wide Assurance; GN, Global Network; ICC, Intra-cluster correlation; ICFI, Infant and Child Feeding Questionnaire; IRB, Institutional Review Board; OHRP, Office for Human Research Protections; SES, Socio-economic status; USDA, United States Department of Agriculture; WHO, World Health Organization.
